### Treatment and follow-up procedures

In the OCT-guided group, OCT imaging will be performed before PCI to appropriately size stent implantation and following stenting to assess the final results and guide further optimization if needed. A final run will be performed at the end of the procedure to confirm optimal results and exclude common causes of stent failure reported in the literature (17). Patients will be given DAPT (oral aspirin 100 mg once daily, clopidogrel 75 mg once daily, or ticagrelor 90 mg twice daily) and will be put on secondary prevention medications according to the recommended ESC guidelines.

Post discharges all patients will have a follow-up appointment or will be contacted by phone at 1 month, 3 months, 6 months, and 1 year. Subjects assigned to O3/A3 arms will undergo coronary angiography and OCT imaging at 3 months, while those assigned to A6 arm will have invasive assessment and OCT imaging at 6 months after the index procedure (Figure 1). The schedule of enrolment, interventions, and assessments is outlined in Figure 2. The data of each center will be summarized and checked by an independent data monitoring committee.

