### Study endpoints

The primary endpoint of the study is the incidence of stent strut coverage (%) at 3- or 6-month follow-up.

The secondary endpoints of the study include angiographic, OCT, and clinical and biomarker outcomes that are listed in Table 3.

**Table 3 tab3:** Endpoints of the trial.

Primary endpoint
The degree of stent struts neointimal coverage (%) at 3 and 6 months
Secondary endpoint
OCT endpoint: Assessed at 3 and 6 months
1. Average and minimal stent diameter, area, and volume.
2. Average and minimal lumen diameter, area, and volume.
3. Average and minimal strut coverage thickness.
4. Strut malposition rate.
5. Vascular repair index.
Clinical endpoints: Assessed at 1, 3, 6, and 12 months
1. Major adverse cardiac events (MACE) composite of cardiac death, target vessel myocardial infarction (TV-MI), and clinical ischemia-driven revascularization.
2. Cardiac death.
3. Non-fatal MI.
4. All revascularization.
5. Target lesion revascularization.
6. Target vessel revascularization.
7. ARC-defined stent thrombosis (early, late, very-late, definite, probable, and possible stent thrombosis).
Molecular biology endpoints: Assessed at baseline, 3 and 6 months
1. Lipid levels (total cholesterol, low-density lipoprotein, high-density lipoprotein, ratio of low-density lipoprotein to high-density lipoprotein, and triglyceride).
2. Molecule indicators (hs-CRP, PTX-3, VCAM-1, and MMP-9).

ARC, academic research consortium; hs-CRP, high sensitive C-reactive protein; PTX-3, pentraxin-3; VCAM-1, vascular cell adhesion molecule-1; and MMP-9, matrix metalloprotein-9.

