### Statistical considerations

The sample size of this study is based on the previously published literature and the corresponding research hypothesis. This study intends to demonstrate that the incidence of strut coverage in the OCT-guided group is higher than that of angiography-guided group at 3-month follow-up (hypothesis 1). The second hypothesis of this study is that the incidence of stent strut coverage in the OCT-guided group at 3 months is similar to the incidence of strut coverage in the angiography-guided group at 6 months (non-inferiority analysis). If the above hypothesis is confirmed then an additional analysis will be performed that aims to demonstrate that the incidence of covered struts is higher at 3 months in the OCT-guided group compared to the rate of strut coverage noted at 6 months in the angiography-guided PCI (hypothesis 3). In order to control for the type I error, the test significance levels of hypothesis 1 and 2 are set at one-sided 0.025. Since hypothesis 3 is a sequential test carried out on the basis of hypothesis 2, the test significance level is set at one-sided 0.05.

The sample size calculation is based on the assumption that each patient will receive on average 1 stents, and that each stent will have a length of 24 mm. OCT analysis will be performed at 0.4/0.6 mm interval and that 7.9 struts in each cross section will be detected. Based on these assumptions, it is estimated that 474 strut results will be obtained from each patient. We estimate that we will need 7,305 strut estimations in each group to prove with 95% power the primary endpoint of the study. Based on the above assumptions, we estimate that 16 patients should be recruited in each group. Considering a 20% drop-off rate, we estimate that 20 patients should be included in each group (Table 4).

**Table 4 tab4:** Parametric assumptions for hypothesis.

	Experimental group coverage	Control group coverage	Non-inferiority margin	Sample size (stent struts)
Hypothesis 1	93.6%	92%	Not applicable	6,781
Hypothesis 2	95%	95%	1.3%	7,305
Hypothesis 3	96.5%	95%	Not applicable	3,912

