Continuous variables will be described as means and SDs if they are normally distributed or median and interquartile range in the case of asymmetric data distribution. Categorical variables will be presented as numbers and percentages. Comparisons of numerical variables are conducted with the Student’s *t* test or Mann–Whitney’ *U* test as appropriate, categorical variables and outcomes were compared by using the chi-squared test or Fisher exact test. A statistical package (SPSS 21.0) will be used for analysis. Two-tailed *p* < 0.05 will be considered statistically significant.

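### Clinical outcomes to 12 months are compared as counts, so the MACE percentage depends on how any patient without 12-month status is counted; a minor point, cheaply improved by reporting cumulative incidence

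*Protocol article*

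**What the plan says.** The general analysis paragraph of Statistical considerations sets both presentation and test: "Categorical variables will be presented as numbers and percentages", and "categorical variables and outcomes were compared by using the chi-squared test or Fisher exact test". The criterion is "Two-tailed *p* < 0.05 will be considered statistically significant". No time-to-event method appears.

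Table 3 under Study endpoints gives the schedule, "Clinical endpoints: Assessed at 1, 3, 6, and 12 months", and defines the composite as "Major adverse cardiac events (MACE) composite of cardiac death, target vessel myocardial infarction (TV-MI), and clinical ischemia-driven revascularization". These are secondary endpoints. None of the three numbered hypotheses concerns them.

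Two further statements bear on loss. The sample size paragraph says "Considering a 20% drop-off rate, we estimate that 20 patients should be included in each group". Treatment and follow-up procedures says that "all patients will have a follow-up appointment or will be contacted by phone at 1 month, 3 months, 6 months, and 1 year". The same section sets the invasive visit: "Subjects assigned to O3/A3 arms will undergo coronary angiography and OCT imaging at 3 months", with the A6 arm examined at 6 months.

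**The concern.** A chi-squared or Fisher test on 12-month events needs a yes or no for every patient at 12 months. A patient last seen event-free at month 5 has neither, so someone must choose a denominator. Two common choices err in opposite directions:

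- Keeping the patient as event-free pulls the risk down.
- Removing only the patients lost without an event, while keeping events seen before loss, pushes it up.

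Neither uses the follow-up time that was observed.

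The 12-month MACE percentage is part of the clinical evidence that will be read beside the article's interest in shorter DAPT. The invasive visit falls at month 3 in O3 and A3 but at month 6 in A6. If patients leave around that visit, the size of the error can also differ between O3 and A6.

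**Working it through.** **The plan's own figure.** The article gives no MACE rate, event count or clinical loss rate. The only loss figure is the 20%, and it belongs to the strut calculation:

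- Struts per patient: 24 / 0.4 × 7.9 = 474.
- Patients: 7,305 / 474 = 15.4, so 16.
- After drop-off: 16 / (1 − 0.20) = 20 per arm.

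This reproduces exactly. The 20% is therefore a stated allowance for OCT data, borrowed below as an assumption for clinical follow-up.

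**Assumptions.** True 12-month risk p of 5 to 20% (not in the document). Probability d of 5 to 20% that a patient's loss time falls within 12 months. Constant hazards, with loss independent of risk.

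**Formulas**, with time in units of 12 months, λ = −ln(1 − p) and μ = −ln(1 − d):

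- Observed events = λ/(λ+μ) × [1 − exp(−(λ+μ))]. This is the reported risk if lost patients count as event-free.
- Lost before an event = μ/(λ+μ) × [1 − exp(−(λ+μ))].
- Reported risk if only event-free losses are removed = observed / (1 − lost before an event).

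**Example, p = 10%, d = 20%.** λ = 0.1054, μ = 0.2231, and 1 − 0.9 × 0.8 = 0.28.

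- Observed = 0.1054/0.3285 × 0.28 = 0.0898.
- Lost = 0.2231/0.3285 × 0.28 = 0.1902.
- Removed version = 0.0898/0.8098 = 0.1109.

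| True risk | Loss | Lost counted event-free | Event-free losses removed | Patients of 20 (true; the two handlings) |
|---|---|---|---|---|
| 5% | 20% | 4.5% | 5.6% | 1.0; 0.90, 1.11 |
| 10% | 5% | 9.75% | 10.2% | 2.0; 1.95, 2.05 |
| 10% | 10% | 9.5% | 10.5% | 2.0; 1.90, 2.10 |
| 10% | 20% | 9.0% | 11.1% | 2.0; 1.80, 2.22 |
| 15% | 20% | 13.5% | 16.6% | 3.0; 2.70, 3.31 |
| 20% | 20% | 18.0% | 22.0% | 4.0; 3.60, 4.39 |

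The error is about 10% relative at 20% loss and 2 to 5% relative at 5 to 10% loss. In patients, it is 0.1 to 0.4 per arm at 20% loss.

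**Kaplan-Meier under the same assumptions.** In 4,000 simulated trials with 20 per arm and 20% independent loss, it averaged 10.1% for a true 10% and 20.0% for a true 20%.

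**Timing of loss, p = 10%, all 20% lost at one visit.**

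- Month 3: risk so far is 1 − 0.9^0.25 = 2.60%. Counted event-free: 2.60 + 0.8 × 7.40 = 8.5%. Event-free losses removed: 8.52 / (1 − 0.2 × 0.974) = 10.6%.
- Month 6: risk so far is 1 − 0.9^0.5 = 5.13%. Counted event-free: 5.13 + 0.8 × 4.87 = 9.0%. Event-free losses removed: 9.03 / (1 − 0.2 × 0.949) = 11.1%.

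O3 and A6 with the same true risk would thus differ by about half a percentage point from visit timing alone.

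**Against sampling error.** With 2 events in 20, the exact 95% CI is 1.2% to 31.7%. A shift of 1 point is far inside it.

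**Limits for unknown status.** With 2 events and 4 of 20 lost event-free, the figure is 2/20 = 10% if all four stay event-free, 2/16 = 12.5% if they are removed, and 6/20 = 30% if all four had events.

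**When loss is related to risk.** If the hazard triples after loss, with 20% loss per arm, Kaplan-Meier gives about 10% against a true 11.8 to 11.9%. With 10% loss in one arm and 30% in the other, it shows 10.1% and 10.1% against a true 11.0% and 12.9%.

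**The case against.** The case against is substantial, and most of it stands as a limit on the claim.

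- **Clinical loss may be small.** A reader might take the 20% as expected clinical loss. The document does not say so. A patient who declines repeat OCT can still be reached by phone at 12 months, and with complete status the count test has no such error.
- **Not every count is biased.** A reader might infer that counts mislead whatever the handling. They do not: excluding every lost patient, including those with an event before loss, is unbiased under independent loss. Its price is that observed events are discarded, which is unattractive in safety reporting.
- **The handling rule may exist elsewhere.** The article does not say how unknown status is counted. That is commonly left to the full protocol or analysis plan, so its absence is no fault. What the article does fix is a count-based comparison of outcomes.
- **Kaplan-Meier is no complete remedy.** It fails in the same direction as counting losses as event-free when patients at higher risk leave. Applied naively to non-fatal components, it also overstates incidence by censoring deaths.
- **Log-rank should not lead.** In the simulations with 20% loss, log-rank rejected more often than Fisher (24% against 13% for 20% versus 5% risk), which makes it tempting. Part of that gap is Fisher's conservatism: with equal 10% risks it rejected 1.1% of the time, against 3.7% for log-rank. Scheduled angiography at month 3 in O3 and A3 and at month 6 in A6 can shift when revascularization is detected, and a log-rank test responds to that timing. A comparison at a fixed 12 months is less sensitive to it, so the protocol's fixed-time approach is defensible.

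These points do not overturn the narrower claim: if any 12-month status is missing, the stated method makes the percentage depend on a counting choice, and a better summary is available for little work.

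**Conclusion.** The point holds as a minor improvement. With 20% loss independent of risk, a true 12-month MACE risk of 10% reads about 9% or about 11% under two usual handlings; smaller loss shrinks the error roughly in proportion, and complete status removes it. The MACE risks, the loss rate applied to clinical follow-up and the loss pattern are all assumptions.

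The documents do not support a stronger conclusion. The endpoints are secondary, carry no hypothesis and play no part in the sample size. The average error is far smaller than the sampling uncertainty at 20 per arm, and strut coverage is unaffected. Nothing here shows that a conclusion of the trial would change.

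**What to change.** In the general analysis paragraph of Statistical considerations, replace the count test for the Table 3 clinical endpoints as follows; Fisher or chi-squared can stay for baseline categories.

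1. Report Kaplan-Meier cumulative incidence from the index procedure at 1, 3, 6 and 12 months with 95% CI, censored at last contact. For non-fatal components, treat death as a competing event and use the cumulative incidence function. Non-cardiac death, which MACE does not include, can be handled in the same way for MACE.
2. Base the between-arm comparison on the 12-month estimate. Keep any log-rank test supportive, because the scheduled angiography falls at different months.
3. State how many patients per arm lack 12-month status, and add a best/worst-case analysis for them.

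The cost is a few sentences and some analysis work. Event dates and last-contact dates must be recorded. The estimate assumes that loss is unrelated to risk, which is why item 3 belongs with it. Power for MACE stays low either way.

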## Discussion

Dual antiplatelet therapy is recommended following stent implantation, but the optimal duration remains controversial in ACS patients, the current ACC/AHA and ESC guidelines recommend DAPT for 12 months after PCI (2, 3). However, prolonged DAPT is associated with worse outcomes in high bleeding risk populations. A consensus from the Academic Research Consortium for High Bleeding Risk (ARC-HBR) defined 14 and six clinical criteria as major or minor criteria, respectively. If patients meet at least one major or two minor criteria, they are considered to be at high bleeding risk (20). According to the ARC-HBR criteria, 40% patients in real-world PCI registry are at high bleeding risk (21). These patients are often excluded from or underrepresented in clinical trials about stents and antiplatelet therapy. The development of advanced stent platforms and the optimal stent deployment—even with the use of intravascular imaging guidance—is expected to enable shorter duration of DAPT in high bleeding risk ACS patients undergoing PCI. Several studies have shown that shorter-term DAPT in ACS patients implanted with next-generation DES is non-inferior to the standard or longer duration of DAPT. More specifically the “all-comer” ITALIC randomized controlled trial demonstrated that after the implantation of next-generation DES, 6-month DAPT followed by aspirin monotherapy is non inferior to 24-month DAPT in terms of all-cause mortality, myocardial infraction (MI), target vessel revascularization (TVR), stroke, and major bleeding in a low risk profile for ischemic events population (22). Similarly, the randomized OPTIMA-C trial (NCT03056118) showed that the MACE rate at 12-month follow-up was not different in patients receiving 6-month DAPT and those treated for 12-month DAPT after implantation of next-generation DES (23). The multicenter REDUCE trial enrolled 1,496 patients admitted with an ACS treated with the next-generation COMBO stent who were randomized to 3-month (*n* = 751) or 12-month (*n* = 745) DAPT. The primary endpoint was a composite of all-cause mortality, MI, ST, stroke, TVR, and bleeding and its incidence was similar in the two groups (8.2 vs. 8.4%, *p* non-inferiority<0.001) at 1- or 2-year follow-up (11.6 vs. 12.1%, *p* = 0.76) (24).

There is compelling evidence that strut coverage is a predictor of ST (25). The next-generation DES with thinner struts, safer polymer profiles and improved drug kinetics appear to enable faster endothelialization and have known to reduce the incidence of ST compared to the first generation DES (25). The OCT sub-study of the OPTIMA-C trial revealed favorable strut coverage at 6 months after next-generation DES implantation (23), similarly the FUNCOMBO trial showed almost complete strut coverage of the next-generation DES in patients who presented with STEMI (26). Moreover, a small study reported that in the biodegradable polymer Synergy stent strut coverage was 94.5% at 3 months and 96.6% at 6 months (27) whereas the TARGET All Comers study showed a similar incidence of strut coverage in biodegradable polymer Firehawk and durable polymer XIENCE stent group (99.9 ± 0.3 vs. 100 ± 0.1%, *p* = 0.26) (28). Conversely, the biodegradable polymer BuMA Supreme stent was found to be superior to the XIENCE stent in terms of strut coverage at both 1 month and 2 months in the PIONEER-II OCT trial (29). However, stent implantation in these studies was mostly performed under angiography guidance. The DETECT-OCT (NCT01752894) trial was the first that highlighted the value of OCT imaging in optimizing stent apposition and in this way accelerating strut coverage. In this trial, the percentage of uncovered struts at 3 months was lower in the OCT-guided group (7.5%) than in the angiography-guided group (9.9%; *p* = 0.009) (8). However, the DETECT-OCT trial mainly included patients suffering from stable angina and did not include the group of patients undergoing OCT at a longer follow-up period. This study was designed to provide additional insights as it aims to include NSTE-ACS patients, and include the group of patients that will undergo OCT imaging at 6 months to examine late strut coverage in patients undergoing angiography guided PCI.

Additionally, clinical studies have found that MACE after PCI not only comes from in-stent restenosis or ST in ACS patients but also due to progression of mild to moderately graded disease in the non-culprit vessels as it is a well-known factor that patients presenting with ACS often have multivessel disease (30, 31). A study involving nearly 13,000 ACS patients showed that over 80% of ischemic events occurring after 30 days were unrelated to the culprit lesion that was stented, but were rather spontaneous, or *de novo* events in a non-culprit vessel (32). Intravascular imaging research revealed that non-culprit lesions in ACS patients are often vulnerable plaques, with characteristics such as thin-cap fibroatheroma and those with heavy lipid load. The progress and rupture of these vulnerable plaques in non-culprit vessels can also result in adverse events like thrombosis after PCI (33, 34). Therefore, understanding the evolution of plaque in non-culprit vessels is of great significance to prevent future adverse cardiac events and may potentially influence decision making in the use of DAPT duration. Thus, our study innovatively performs OCT examination in both culprit and non-culprit vessels at baseline and follow-up, to explore vulnerable plaque progression in non-target vessels, measure the changes in the thickness of the fibrous cap over lipid-rich plaques, and examine changes in macrophages accumulations and in the lipid content and in the vulnerable plaques, and their transformation at various time points. Furthermore, plaque progression is usually accompanied with lipid infiltration and inflammatory response. The positive correlation of cholesterol levels, proinflammatory cytokines, and atherosclerotic evolution is well established (35). Stent implantation is associated with vessel wall injury and endothelium disruption while it is well known that strut polymer and drug elution can trigger a pro-inflammatory and hypersensitivity reaction leading to the formation of neoatherosclerotic lesions (34). There are however limited data about the association between vulnerable plaque progression in native segments and neointima proliferation and neoatherosclerotic lesion formation in segments treated with stents. The present study has been designed to provide additional insights and explore the implications of the lipid profile and systemic inflammation assessed by circulatory biomarkers on neointima characteristics and atherosclerotic disease progression in native segments.

This study has several limitations. Firstly, only three centers in Huaihai economic zone are participated in this study. Therefore, the findings of this analysis may not be relevant to other populations. Secondly, “different operators” experience may impact the procedure outcomes, which is the source of uncontrolled bias. Finally, several studies revealed that the early strut coverage of biodegradable polymer DES is not similar with other next-generation DES (36, 37), which implies the results of our study may not be simply generalized to other DES with different design concept.

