11. Participation in other clinical trial.
12. Poor compliance, unable to provide written informed consent.
13. Heart transplantation.
14. Undergoing chemotherapy or immunosuppressive therapy.
15. Elective surgery requiring stopping anti-platelet therapy within half a year post stent implantation.
16. Platelet count lower than 100 × 10^9^/L, or more than700 × 10^9^/L, and white blood cell lower than 3 × 10^9^/L, liver diseases (such as hepatitis).

OCT, optical coherence tomography; eGFR, estimated glomerular filtration rate

The recruited patients will be randomized at 1:1:1 ratio to three groups using a computer-generated random sequence table. Patients enrolled in the first group will have OCT-guided revascularization and 3-month follow-up OCT imaging (O3 group, *n* = 20), those in the second group angiography-guided PCI and 3-month follow-up OCT imaging (A3 group, *n* = 20) while the patients recruited in the third group angiography-guided PCI and 6-month follow-up OCT imaging (A6 group, *n* = 20).

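### Operator differences are called uncontrolled, yet the named tests leave out centre, which is known for every patient; adding it is a cheap, minor improvement

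*Protocol article*

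**What the plan says.** In the limitations paragraph of the Discussion, the article expects operators to influence results: their "experience may impact the procedure outcomes, which is the source of uncontrolled bias". The same paragraph notes that "only three centers in Huaihai economic zone are participated in this study", but only as a limit on generalisability.

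Under Patient enrollment and randomization, patients are "randomized at 1:1:1 ratio to three groups using a computer-generated random sequence table". Stratification by centre is neither stated nor excluded.

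Under Statistical considerations, the sentence beginning "Comparisons of numerical variables are conducted with the Student’s" names the t test or Mann-Whitney test for continuous variables, and then "categorical variables and outcomes were compared by using the chi-squared test or Fisher exact test". None of these, as named, has a term for centre or operator. In the same section "the test significance levels of hypothesis 1 and 2 are set at one-sided 0.025". Hypothesis 1 is sized on 93.6% against 92% coverage, and hypothesis 2 on a 1.3-point non-inferiority margin. Sixteen evaluable patients per group are planned.

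**The concern.** The article names a source of variation that it expects to matter, calls it uncontrolled, and then lists only tests that cannot take account of any part of it. Centre is recorded for every patient and is a reasonable partial proxy for operator. Under QCA and OCT data acquisition and analysis, angiography-guided stenting follows local standard practice and the operator's visual assessment, and antithrombotic therapy follows the local protocol. Two of the three arms are therefore delivered largely by local habit.

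The targets are small: 1.6 points for hypothesis 1 and a 1.3-point margin for hypothesis 2. With 16 evaluable patients per arm, the mix of centres can differ between arms by chance. If centres differ in coverage, an unadjusted comparison carries that difference as noise. At stake is some precision in the primary contrasts, and an admitted limitation that is wider than it needs to be.

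**Working it through.** **The plan's own figures.** All reproduce, treating struts as independent.
- Hypothesis 1, one-sided 0.025, 95% power: n = [1.960·√(2·0.928·0.072) + 1.645·√(0.936·0.064 + 0.92·0.08)]² / 0.016² = 6,781 struts per group.
- Hypothesis 2: n = (1.960 + 1.645)²·2·0.95·0.05 / 0.013² = 7,305.
- Hypothesis 3, one-sided 0.05: the formula of hypothesis 1 with 96.5% and 95% gives 3,912.
- Patients: 24/0.4 × 7.9 = 474 struts each; 7,305/474 = 15.4, so 16; 16/0.8 = 20 enrolled.

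No stated figure is wrong.

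**Size of a chance centre shift.** Assumptions, none given in the article: simple randomisation, three centres of equal size, and centre means evenly spaced with best-to-worst spread R (at -R/2, 0, +R/2).
- Between-centre variance = [(R/2)² + 0 + (R/2)²]/3 = R²/6.
- SD of the shift in an arm contrast = √(2 × (R²/6)/16) = R/√48 = 0.144·R.

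The SDs agree with 100,000 simulated draws, which also give the probabilities:

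| Spread R (points) | SD of shift | As share of 1.6 | As share of 1.3 | P(shift ≥ 0.8) | P(shift ≥ 0.65) | P(shift ≥ 1.3) |
|---|---|---|---|---|---|---|
| 1 | 0.14 | 9% | 11% | 0% | 0% | 0% |
| 2 | 0.29 | 18% | 22% | 0.6% | 2% | 0% |
| 3 | 0.43 | 27% | 33% | 6% | 16% | 0.3% |
| 4 | 0.58 | 36% | 44% | 16% | 23% | 2% |

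Here 0.8 is half the hypothesis 1 effect and 0.65 is half the hypothesis 2 margin.

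**What the shift does to the test.**
- *Patient-level test.* The between-centre variance is part of the observed spread between patients, so it is already in the standard error. In simulation the t test keeps its nominal one-sided 0.025. Only precision is lost.
- *Strut-level test with struts taken as independent.* At 92% coverage and 7,305 struts per group the standard error is 100·√(2·0.92·0.08/7,305) = 0.45 points, which leaves out the centre shift. Centre imbalance alone would then raise one-sided 0.025 to about 0.03, 0.05, 0.08 and 0.11 at spreads of 1, 2, 3 and 4 points.

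**What the centre term gains or costs.** Write s for the within-centre SD of patient-level coverage, assumed to be 3 to 5 points. The unadjusted standard error exceeds the within-centre one by a factor √(1 + R²/(6s²)).
- At R = 4, s = 3: √(1 + 16/54) = 1.14.
- At R = 4, s = 5: √(1 + 16/150) = 1.05.

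In simulation, fitting the term costs about 2-3% in standard error when centres do not differ. The net gain reaches roughly 10% at a 4-point spread.

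**The case against.** The strongest reply is that this is a condensed article. Stratification factors and model covariates are commonly left to the full protocol or analysis plan, so their absence is no error. That stands for stratification, and a reader should not infer that allocation ignored centre. It stands less well for the analysis: the article does name its tests, and it does call the operator effect uncontrolled. A centre term in an unseen plan would make that word too strong.

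Second, the limitation concerns operators, not centres. The number of operators per centre is not given, and a centre term leaves differences within a centre untouched. This stands: centre is a partial proxy only.

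Third, a reader might infer that the contrasts will be biased, or that chance imbalance will move them by a large share of 1.6 or 1.3 points. The documents support neither. Chance imbalance under randomisation is variance, and no between-centre spread is given. The only scale in the article is indirect. In the Discussion, the cited trial of OCT against angiography guidance shows 9.9 - 7.5 = 2.4 points, and the cited three- against six-month coverage shows 96.6 - 94.5 = 2.1 points. A centre spread of 3 points would exceed both. At 2.4 points the SD of the shift is 0.144 × 2.4 = 0.35, or 22% of 1.6. All images are read in an independent core laboratory, so local reading should not add to the spread.

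**Conclusion.** The concern holds as a minor point. The named tests carry no centre term, although the article itself expects an operator effect and centre captures part of it. The consequence is a possible loss of precision, conditional on an undocumented spread: negligible at 1 to 2 points (shift SD 0.14 to 0.29) and material only at about 3 points or more (SD 0.43 and above). These figures assume simple randomisation, three equal centres and 16 patients per arm.

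A patient-level comparison remains valid without the term. Type I error is inflated only if struts are tested as independent observations. Clustering of struts within patient is a separate and larger issue, and a centre term does not address it.

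**What to change.** Analyse the two planned contrasts, O3-A3 (hypothesis 1) and O3-A6 (hypotheses 2 and 3), on patient-level coverage with centre (three levels) as a fixed effect. For hypothesis 2, compare the confidence limit of the centre-adjusted difference with the 1.3-point margin.

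Reword the limitation: centre is adjusted for, and operator differences within centre remain.

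The cost is a change of wording in the analysis plan, two degrees of freedom out of about 3 × 16 = 48 evaluable patients, and standard errors about 2-3% wider if centres turn out not to differ. No extra data or patients are needed.
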